### Criteria for reoperation

Reoperation is indicated when the following two criteria are simultaneously fulfilled:(i)Neurological symptoms are present that are considered to be caused by ipsilateral CSDH.(ii)The hematoma has increased in size compared to immediately after surgery and compressed the brain parenchyma in CT scans.

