### Sample size {14}

The present study aimed to recruit 1186 cases, with 593 patients allocated to each group. The target number of cases was determined based on a previous meta-analysis that examined the efficacy of irrigation for CSDH. A meta-analysis reports a recurrence proportion of 8.06% (38/471) in the irrigation group and 13.05% (59/452) in the non-irrigation group; however, this difference was not statistically significant [17]. The 95% confidence intervals were 5.8–10.9% for the irrigation group and 10.1–16.5% for the non-irrigation group. To account for the differences in outcome measures between the prior and present studies, we set the proportions of patients meeting the criteria for ipsilateral reoperation at 7% for the irrigation group and 12% for the non-irrigation group. Using *α* = 0.05 and *β* = 0.20 and accounting for a 10% dropout proportion, a total of 1186 cases, with 593 cases in each group, have been calculated to be necessary for the current study. In determining the sample size, the sample size calculation tool for 2 × 2 contingency tables by Kazuhiko Nagashima was used [35] (https://nshi.jp/contents/js/twofreq/).

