### Plans to promote participant retention and complete follow-up {18b}

If the patient does not attend according to the established schedule, the study investigator will contact the patient or family member to ask about the situation and whether the investigator can provide assistance to avoid future missed sessions. If the patient cannot visit for the 6-month postoperative assessment of the primary outcome, the status would be checked telephonically.

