## Statistical methods

### Statistical methods for primary and secondary outcomes {20a}

A statistician blinded to the treatment assignments will perform the analysis. For the primary endpoint, we will adhere to the intention-to-treat (ITT) principle; all patients who have been randomized and underwent surgery will be analyzed according to the group they were allocated to, irrespective of the treatment they received. When outcomes are missing for these patients, they will be treated as not having met the criteria for reoperation. The comparison for this endpoint between the two groups will be made using Fisher’s exact test. As a secondary analysis, the odds ratio estimates and their 95% confidence intervals will be calculated for the primary endpoint and secondary endpoints of the proportion of reoperations, the proportion of deaths, and the proportion of surgery-related complications. For the secondary endpoints of mRS, change in GCS, time from surgery to discharge, and operative time, the two groups will be compared by calculating the mean difference between the groups and its 95% confidence interval. 95% confidence intervals will be calculated using the Clopper-Pearson and bootstrap methods, respectively.

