### Methods in analysis to handle protocol nonadherence and any statistical methods to handle missing data {20c}

If a significant amount of data is missing for any of the secondary endpoints or other analyses, we will conduct exploratory analyses to assess the impact of the missing data.

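### Missing primary outcomes are scored as the favourable result, and the protocol states no check of that rule for the confirmatory test; the bias is small for modest imbalance in loss and material for large or outcome-related imbalance

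*Protocol article*

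**What the plan says.** All references are to the protocol article. Under Statistical methods for primary and secondary outcomes (20a), the primary analysis set is described thus: "all patients who have been randomized and underwent surgery will be analyzed according to the group they were allocated to". For patients in that set without an outcome, "When outcomes are missing for these patients, they will be treated as not having met the criteria for reoperation". The test is fixed as well: "The comparison for this endpoint between the two groups will be made using Fisher’s exact test".

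The section on nonadherence and missing data (20c) is conditional and names its scope: "If a significant amount of data is missing for any of the secondary endpoints or other analyses", exploratory analyses will assess the impact. The primary endpoint is not named. Section 20b allows further exploratory analyses if needed, without specifying any.

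The endpoint has two parts that must hold at the same time: neurological symptoms attributed to the ipsilateral hematoma, and an imaging part, "The hematoma has increased in size compared to immediately after surgery and compressed the brain parenchyma in CT scans". For patients who cannot attend at 6 months, section 18b says "the status would be checked telephonically". The note to Fig. 1 requires imaging at 6 months when symptoms are worsening and does not always require it when they are stable.

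Neither patients nor staff are blinded (17a), and treating physicians assess outcomes (8). The sample size section (14) assumes "7% for the irrigation group and 12% for the non-irrigation group" and 10% dropout, with no split by arm. Section 31c announces a SAP before data lock; it is not shown.

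**The concern.** The rule is a deliberate choice for the primary test, so it is not a detail left open for the SAP. It replaces each unknown outcome by the favourable value with no allowance for uncertainty. If the arms lose different proportions of patients, or lose patients at different risk, the arm with more unseen events looks better than it is. Open-label follow-up makes unequal loss possible, and section 11b lets patients withdraw after learning their allocation.

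At stake is whether a positive or a null result can be trusted when nothing stated in the protocol shows how far it depends on the assumption. The central double-check of reoperation decisions (5d) reviews decisions that were recorded; it cannot recover an outcome that nobody observed.

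**Working it through.** **Inputs.** From section 14: 7% (irrigation) and 12% (control), alpha 0.05, power 0.80, dropout 10%, 593 per arm. From 20a: Fisher's exact test, missing = not met. Assumed here: the split of loss by arm, and the share of lost patients' events seen before loss.

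**The plan's own figure.** The two-sided normal-approximation formula for two proportions without continuity correction gives 539 per arm. 539 x 1.10 = 592.9, so 593 per arm and 1186 in total. The stated size reproduces.

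**Formula.** Let m be the proportion with a missing outcome and r the event rate among those patients. The analysed rate is p - m x r. Writing the benefit as control minus irrigation, the spurious part is

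bias = (m x r, irrigation) - (m x r, control).

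If loss is unrelated to outcome and no lost patient's event is seen, r = p and the analysed rate is p(1 - m). If half of those events are seen before loss, replace m by m/2. Power and type I error below come from exact enumeration of the two-sided Fisher test at 593 per arm.

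**No true effect, 12% in both arms**

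| Loss, irrigation / control | Analysed rates | Spurious difference | Type I error |
|---|---|---|---|
| 0 / 0 | 12% / 12% | 0 | 4.1% |
| 10% / 10% | 10.8% / 10.8% | 0 | 4.0% |
| 12% / 8% | 10.56% / 11.04% | 0.48 points | 4.7% |
| 15% / 5% | 10.2% / 11.4% | 1.2 points | 8.6% |
| 15% / 5%, half the events seen | 11.1% / 11.7% | 0.6 points | 5.1% |
| 15% / 5%, event rate among the missing 24% | 8.4% / 10.8% | 2.4 points | 25.7% |

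In the last row the overall rate is still 12% in both arms: 12% - 0.15 x 24% = 8.4% and 12% - 0.05 x 24% = 10.8%.

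**Planned effect, 7% and 12%**

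| Loss, irrigation / control | Analysed rates | Difference | Power |
|---|---|---|---|
| 0 / 0 | 7% / 12% | 5.0 points | 81.6% |
| 10% / 10% | 6.3% / 10.8% | 4.5 points | 76.7% |
| 5% / 15% | 6.65% / 10.2% | 3.55 points | 56% |
| 15% / 5% | 5.95% / 11.4% | 5.45 points | 90% |

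With half the events seen, the last two rows become 70% and 86%.

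**How much of the power loss is due to the rule.** Dropping the missing 10% leaves 534 per arm at 7% and 12%, with power 77.1%. Of the fall from 81.6% to 76.7% (4.9 points), 4.5 points would occur anyway and 0.4 points belong to the rule.

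**Tipping example.** Take 59 missing per arm and the planned rates among the 534 observed: 37 and 64 events. Under the rule, 37/593 against 64/593 gives p = 0.007. Adding 7 events among the missing irrigation patients (7/59 = 12%) and none among the missing controls gives 44/593 against 64/593, p = 0.055. Adding 7 events to both arms gives 44/593 against 71/593, p = 0.010. The conclusion is therefore sensitive to a difference between the missing groups, and much less to a rate they share.

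**The case against.** The strongest reply is that sensitivity analyses are normal SAP content, the SAP is still to come, and sections 20b and 20c leave room for further work. That stands in part: a reader may not infer that the primary rule will never be tested. What remains is that the protocol itself chose the rule and then wrote a missing-data section whose stated scope passes over the primary endpoint.

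Four stronger readings are tempting, and the document does not support them.

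- That any difference in loss becomes a treatment effect of similar size. Only the event-rate share carries over, about 12% of the imbalance at the control rate. A 4-point gap is nearly harmless.
- That 10% dropout outweighs a 5-point effect. A dropout proportion has to be multiplied by an event rate before it can be compared with a risk difference. Nor does section 14 say that all of the 10% would be missing primary outcomes among operated patients.
- That the rule costs the trial its power under equal loss. Almost all of that cost is ordinary dropout.
- That a phone contact always scores falsely as a success. A patient without symptoms fails the first criterion and is correctly not met without a CT. The telephone check reduces missingness. The gap is confined to a patient who reports symptoms by phone and has no CT or outside record.

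It is also fair to say that the 5% and 15% split has no source in the document, and that multiple imputation has its own untestable assumption (missing at random) and does not combine directly with Fisher's test. This argues for imputation as a sensitivity analysis and against replacing the primary analysis.

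**Conclusion.** The concern holds in a limited form. The protocol scores every missing primary outcome as the favourable one and states no check of that rule for the confirmatory test. The bias can go in either direction. It is about 0.5 points (type I error 4.7%) for losses of 8% and 12%, and 1.2 points (8.6%) for an assumed 5% and 15% with no lost patient's event seen, falling to 5.1% if half are seen. It grows if loss is related to outcome. Under the planned effect, the 5% and 15% split moves power to 56% or 90%. Equal loss only shrinks the difference, from 5.0 to 4.5 points at 10%.

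These sizes rest on assumed splits of loss and on the planned event rates. The document does not show that unequal loss will occur, and the unseen SAP may already contain a check. The point is that the confirmatory result should not depend on a favourable assumption that nothing stated in the protocol tests.

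**What to change.** Extend section 20c to the primary endpoint and carry it into the SAP before data lock:

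1. Report the number and proportion of missing primary outcomes by arm.
2. Keep the Fisher analysis under the present rule if wished, and prespecify a multiple-imputation analysis by arm, using the minimisation factors and the 72-hour and 4-6-week status, all of which are already collected.
3. Add a tipping-point table over event rates assumed for the missing in each arm, varied separately. State that the primary conclusion is called robust only if it survives plausible values.
4. Define the coding of telephone follow-up. A contact who reports symptoms but has no CT or outside record is recorded as missing, not as observed not met; a symptom-free contact remains not met. This makes such cases visible to items 1 to 3.

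The cost is a short amendment to the analysis text, an imputation model to specify, and some additional analysis. No new data collection is needed. The real downside is that the conclusion may have to be stated less firmly if the result proves fragile.

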*Abbreviations*: *CSF* cerebrospinal fluid, *ACF* artificial cerebrospinal fluid, *NS* normal saline, *LR* lactated Ringer’s solution

Furthermore, various factors like age, antithrombotic therapy, alcoholism, and pre- and postoperative computed tomography (CT) have been identified as recurrence risks, underscoring the need for a comprehensive approach to studying CSDH recurrence [19–25].

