### Trial design {8}

This study is a prospective, multicenter randomized, controlled, non-blinded trial. This study evaluates intraoperative irrigation via ACF with a subdural drain versus a subdural drain alone after the evacuation of a CSDH. Except for randomization to irrigation versus no irrigation, the management of the study participants will not differ from the current management of patients. A 1:1 stratified randomization will be performed at each site using a web-based system. Clinical symptoms and imaging assessments will be conducted by the treating physicians at each facility, following the timeline of the participants.

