## Assignment of interventions: allocation

### Sequence generation {16a}

Randomization was performed using a minimization method of balancing age (69 years or younger vs. 70 years or older), hematoma architecture on CT scans (homogeneous, stratified, isolated, and trabecular), the presence of antiplatelet therapy, preoperative GCS score (13 or lower vs. 14 or higher), and institution at baseline in a 1:1 ratio. If there is a small contralateral hematoma, only the hematoma architecture is considered when performing surgery.

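### The primary comparison is a crude Fisher's exact test although allocation is minimised on five factors: power is lost, mostly to Fisher's conditioning and a little to ignoring the factors

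*Protocol article*

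**What the plan says.** The section on statistical methods for primary and secondary outcomes {20a} names the primary test outright: "The comparison for this endpoint between the two groups will be made using Fisher’s exact test". Odds ratios with 95% confidence intervals follow as a secondary analysis, with no covariates mentioned. The section on additional analyses {20b} adds only unspecified exploratory work.

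Sequence generation {16a} describes the allocation: "Randomization was performed using a minimization method of balancing age (69 years or younger vs. 70 years or older"), then "hematoma architecture on CT scans (homogeneous, stratified, isolated, and trabecular"), then "the presence of antiplatelet therapy, preoperative GCS score (13 or lower vs. 14 or higher"), and finally "institution at baseline in a 1:1 ratio". Trial design {8} describes the same step differently: "A 1:1 stratified randomization will be performed at each site using a web-based system".

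On prognosis, Background and rationale {6a} says that "various factors like age, antithrombotic therapy, alcoholism, and pre- and postoperative computed tomography (CT) have been identified as recurrence risks". The Discussion adds that recurrence varies with the internal architecture of the haematoma. The sample size {14} assumes "7% for the irrigation group and 12% for the non-irrigation group", α = 0.05, 80% power and 10% dropout, giving 593 per arm and 1186 in total.

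**The concern.** Factors chosen for balancing are normally carried into the primary analysis. If they predict the outcome, balancing them makes the arms more alike than an unadjusted test assumes, and that test then tends to reject too rarely. Fisher's exact test is also conservative in its own right, because it conditions on the total number of events and its p-values are discrete. Both effects work in the same direction. What is at stake is power: the chance of detecting the planned 5-point difference with the 1186 patients recruited. The two causes need to be separated, because they differ in size and in how firmly the documents support them.

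**Working it through.** **1. Reproduce the planned sample size.** Inputs from Sample size {14}: p₁ = 0.07, p₂ = 0.12, mean 0.095, difference 0.05, 80% power. Sidedness is not stated; two-sided α = 0.05 is taken because only that reproduces the total.

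n = [1.960·√(2·0.095·0.905) + 0.8416·√(0.07·0.93 + 0.12·0.88)]² / 0.05²
= (0.8127 + 0.3477)² / 0.0025 = 538.7, so 539 per arm.

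539 × 1.10 = 592.9, so 593 per arm and 1186 in total: an exact match. The continuity-corrected formula, which approximates Fisher's test, gives 578 per arm before dropout and 636 after × 1.10, so it does not match. The trial was sized for the uncorrected chi-square test.

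**2. Exact size and power without covariates.** For each pair of event counts (a, b), take the product of the two binomial probabilities and sum over all pairs with two-sided p ≤ 0.05. No assumption about covariates is needed.

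| Setting | Fisher | Uncorrected chi-square |
|---|---|---|
| Size, 534 per arm, null rate 7% / 9.5% / 12% | 0.038 / 0.039 / 0.040 | 0.050 / 0.050 / 0.050 |
| Size, 593 per arm, null rate 9.5% | 0.040 | 0.049 |
| Power, 7% vs 12%, 534 per arm (593 × 0.90) | 77.1% | 80.2% |
| Power, 7% vs 12%, 593 per arm | 81.6% | 84.0% |
| Power, 593 per arm, 10% missing counted as non-events (0.9 × 7% = 6.3%, 0.9 × 12% = 10.8%) | 76.7% | 79.5% |

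Fisher's conditioning alone therefore costs 80.2 − 77.1 = 3.1, 84.0 − 81.6 = 2.4 and 79.5 − 76.7 = 2.8 points. Fisher's test first reaches 80% power at about 572 evaluable patients per arm.

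**3. What the covariates add.** This was simulated with 1068 patients (2 × 534), minimisation on the five factors, and a logistic model with treatment and the four patient-level factors. Each scenario had 8000 null and 6000 alternative runs. The following are assumptions, not in the documents: a biased coin of 0.8; 75% aged 70 or older, 20% on antiplatelets, 15% with GCS 13 or lower; architecture 40/20/25/15%; 19 equal sites; and the covariate odds ratios. Monte Carlo error is about 0.2 points for size and 0.5 for power.

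| Assumed covariate effects | Size: Fisher / chi-square / adjusted | Power: Fisher / chi-square / adjusted |
|---|---|---|
| None | 4.0 / 4.8 / 4.8% | 78.0 / 80.3 / 80.1% |
| Moderate (ORs about 1.5–2) | 4.2 / 5.1 / 5.2% | 77.7 / 80.0 / 80.5% |
| Strong (ORs about 2–4) | 4.0 / 5.0 / 5.5% | 80.0 / 82.4 / 84.0% |

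Moving from Fisher to chi-square gains 2.3 to 2.4 points in every row. Moving from chi-square to the adjusted model gains about 0, 0.5 and 1.6 points. The crude chi-square test stays close to 5% under the null throughout, so the conservatism from forced balance is too small to see at these event rates.

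**4. Institution.** In a separate simulation with 1186 patients (1500 runs per setting, its own assumed effects), a model with the four factors plus site indicator variables rejected a true null in 5.3–6.7% of trials. About 593 × (0.07 + 0.12) = 113 events over 19 sites is roughly 6 per site, too few to support that model.

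**The case against.** The strongest reply is that Fisher's test is valid: it holds type I error at or below 5%, and with all 593 patients per arm evaluable it has 81.6% power, above the 80% target. Replacing it gives up that guarantee. Most of the lost power would also return by switching to an unadjusted chi-square test. All of this is true. It limits the point to efficiency, but does not remove the shortfall at the plan's own 10% dropout.

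It can also be said that adjusted analyses belong to the statistical analysis plan, which the article promises before data lock. That would answer a complaint that an adjusted analysis is missing. It does not answer this point, because the article itself fixes the primary test.

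Four stronger readings are tempting and are not supported:

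- **That ignoring the minimisation factors is the main cause.** The calculations show the reverse order.
- **That the reported interval is too wide.** No interval width was computed, and adjustment in a logistic model does not shrink the standard error of the conditional odds ratio. A precision gain applies literally only to a marginal measure, such as a standardised risk difference.
- **That all five factors are documented predictors.** The article supports age, antithrombotic therapy (of which antiplatelet therapy is part) and CT findings. It does not say that GCS or institution predicts recurrence.
- **That the term stratified randomisation in Trial design {8} reveals a second allocation scheme.** Sequence generation {16a} gives the method in full, so this is an editorial matter.

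**Conclusion.** The point holds as a matter of efficiency. The primary test ignores factors that are balanced by design and already recorded, and it is conservative. Leaving Fisher's test recovers 2.4 to 3.1 points of power by exact calculation, resting only on the planned event rates and numbers of patients. Adjusting for the four patient-level factors adds about 0 to 1.6 points, and that part rests wholly on assumed covariate effects. At the planned dropout the stated test has about 77% power against the intended 80%; with complete follow-up it exceeds the target. A reader might infer that the trial's error control is compromised, but the error lies on the safe side. A change is worth making because it needs no extra patients or data.

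**What to change.** Make the primary analysis a logistic regression of the endpoint on allocated group, adjusted for age group, haematoma architecture, antiplatelet therapy and GCS group as entered at registration. Report a covariate-standardised risk difference with its 95% CI, and say whether the test of the treatment coefficient or that interval decides the result. Keep Fisher's exact test as a supportive analysis.

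Do not add 19 site indicators. Include institution only as a random intercept or in a sensitivity analysis, and only after its size has been checked by simulation, since neither that model nor the interval for the standardised risk difference was simulated here. In Trial design {8}, call the allocation method minimisation.

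The cost is protocol and analysis-plan wording, settled before data lock and without sight of outcomes by arm, plus slightly more analysis work. The concealment section {16b} requires the factors to be entered before surgery, so no new data are needed. The real downside is losing Fisher's guaranteed size: the adjusted test had simulated size of about 0.048–0.055, and the highest value, under strong assumed effects, lies slightly above nominal.

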### Outcomes {12}

#### Assessment items

The demographic information collected includes age, sex, medical history, lifestyle history, and traumatic episodes that may have contributed to the condition. Patients’ living situations, whether at home, in a hospital, rehabilitation center, or nursing home, are to be recorded as well.

Neurological status is to be assessed using the modified Rankin Scale (mRS), Glasgow Coma Scale (GCS), Markwalder classification, and any existing neurological symptoms. The modified Rankin Scale (mRS) was developed to evaluate the severity of stroke outcomes. However, its application extends to clinical assessments of CSDH [30–32]. This scale ranges from 0, denoting the absence of symptoms, to 6, which signifies death (Table 2). GCS is used to objectively express the degree of impairment of all types of consciousness in terms of the three aspects of eye-opening, motor, and verbal reactions (Table 3). The Markwalder classification divides the severity of symptoms of CSDH into 0–4 [33] (Table 4). The scores on these scale at will be determined by physicians who were trained to obtain them.

**Table 2 Tab2:** Modified Rankin Scale (mRS)

Score	Description
0	No symptoms
1	No significant disability: Despite symptoms, able to carry out all usual duties and activities
2	Slight disability: Unable to perform all previous activities but able to look after own affairs without assistance
3	Moderate disability: Requiring some help but able to walk without assistance
4	Moderately severe disability: Unable to walk without assistance and unable to attend to own bodily needs without assistance
5	Severe disability: Bedridden, incontinent, and requiring constant nursing care and attention
6	Death

**Table 3 Tab3:** Glasgow Coma Scale (GCS)

Eye opening		Verbal response		Motor response	
Score	Description	Score	Description	Score	Description
4	Eyes open spontaneously	5	Orientated	6	Obeys commands
3	Eye opening to sound	4	Confused	5	Localizing pain
2	Eye opening to pain	3	Inappropriate words	4	Withdrawal from pain
1	No eye opening	2	Incomprehensible sounds	3	Abnormal flexion to pain
		1	No verbal response	2	Abnormal extension to pain
				1	No motor response

**Table 4 Tab4:** Markwalder classification

Grade	Description
0	Patient neurologically normal
1	Patient alert and oriented; mild symptoms such as headache; absent or mild neurological deficit, such as reflex asymmetry

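### The secondary endpoint is GCS at 6 months, but the analysis section compares change in GCS without naming the visits

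*Protocol article*

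**What the plan says.** In the protocol article, the section Secondary endpoints lists three scales together, each as its value at 6 months: mRS, GCS and Markwalder grade. It lists no change score.

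The section Statistical methods for primary and secondary outcomes {20a} then states: "For the secondary endpoints of mRS, change in GCS, time from surgery to discharge, and operative time, the two groups will be compared". The measure of effect is a difference in means with a 95% interval. On how the intervals are obtained, the section adds: "95% confidence intervals will be calculated using the Clopper-Pearson and bootstrap methods, respectively". Read in order, the bootstrap belongs to the mean differences. No visit is attached to mRS or to the change in GCS, no covariate is named, and Markwalder does not appear.

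Two other places matter. Preoperative GCS is a minimisation factor: "preoperative GCS score (13 or lower vs. 14 or higher), and institution at baseline in a 1:1 ratio". Participant timeline {13} schedules data collection before surgery, within 72 h after it, at 4–6 weeks and at 6 months, among other points.

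**The concern.** A value at 6 months and a change are different variables, and only the first is a listed endpoint. With several scheduled visits, the change could start before surgery or within 72 h after it, and could end at 4–6 weeks or at 6 months. The choice of start matters. A preoperative start is a true baseline. A start within 72 h after surgery comes after the irrigation has been done or withheld, so subtracting it could remove part of any treatment effect.

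The trial is not blinded, and the treating physicians make the clinical assessments (Trial design {8}; Who will be blinded {17a}). The variable should therefore be fixed before anyone examines results. The statistician is to be blinded to assignment, which helps but does not settle which variable is meant.

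The second cost is precision. Even with the natural reading (6 months minus preoperative), a raw change score is generally a less efficient use of the baseline than adjusting for it.

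**Working it through.** **The two sections side by side**

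| Scale | Secondary endpoints | Statistical methods {20a} |
|---|---|---|
| mRS | value at 6 months | mean difference, no visit named |
| GCS | value at 6 months | mean difference in change, no visits named |
| Markwalder | value at 6 months | not named |

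The GCS row is a contradiction. The mRS row is an omitted time point that the endpoint list supplies. The Markwalder row is a silence.

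**The plan's own figure.** The documents give no figure for these scales. The stated sample size belongs to the primary endpoint and rests on "we set the proportions of patients meeting the criteria for ipsilateral reoperation at 7% for the irrigation group and 12% for the non-irrigation group" and "Using *α* = 0.05 and *β* = 0.20". A two-sided comparison of 7% with 12% at 80% power, without continuity correction, needs 539 per arm. Then 539 × 1.10 = 592.9, so 593 per arm and 1186 in total, as stated. Nothing below changes that.

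**Precision of change against baseline adjustment.** Let r be the correlation between preoperative and 6-month GCS. The documents do not give it, so 0.2 to 0.5 is assumed. With equal variances at the two visits, and relative to an unadjusted 6-month comparison:

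- change score: 2(1 − r)
- baseline-adjusted 6-month value: 1 − r²
- ratio of change to adjusted: 2(1 − r)/(1 − r²) = 2/(1 + r)

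| r | change | adjusted | change ÷ adjusted |
|---|---|---|---|
| 0.2 | 1.60 | 0.96 | 1.67 |
| 0.3 | 1.40 | 0.91 | 1.54 |
| 0.5 | 1.00 | 0.75 | 1.33 |

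So a change-score analysis would need 67%, 54% or 33% more patients to match the adjusted one. At r below 0.5 it is also less precise than ignoring the baseline altogether.

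**If the variances differ.** Let k be the preoperative SD divided by the 6-month SD. The change score then has relative variance 1 + k² − 2rk. The difference from 1 − r² is (k − r)², which is never negative. The direction therefore does not depend on equal variances, but the size does. At r = 0.3:

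- k = 2: 1 + 4 − 1.2 = 3.8 against 0.91, a ratio of 4.18
- k = 0.5: 1 + 0.25 − 0.3 = 0.95 against 0.91, a ratio of 1.04

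**mRS.** The plan does not analyse mRS as a change, so the relevant gain is that of an adjusted over an unadjusted 6-month comparison, 1/(1 − r²): 1.04 at r = 0.2, 1.10 at r = 0.3 and 1.33 at r = 0.5. That is about 4% to 33%.

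**The case against.** The strongest defence is that this is one loose phrase about one secondary endpoint in a condensed article. Plans to give access {31c} promises an SAP before data lock that will govern all analyses, and it may already resolve the phrase. If change means 6 months minus preoperative and data are complete, randomisation gives change and 6-month GCS the same expected difference between arms. That limits the consequence. It does not remove the mismatch, because the article fixes two different variables for one endpoint.

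Several stronger readings are tempting, and the documents do not support them.

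- *Markwalder will get no result.* The article names no method for it, but does not say it will go unanalysed. The SAP may supply one.
- *Means of ordinal scales are invalid.* mRS is ordered ("This scale ranges from 0, denoting the absence of symptoms, to 6, which signifies death"), but a mean difference with a bootstrap interval is a valid comparison that needs no normality. A proportional-odds model would be a preference and brings its own assumption. In a simulation with an assumed skewed mRS distribution, a common odds ratio of 1.35 and 533 per arm, power was about 74% for means and 79% for a rank test, a modest gap. Markwalder is also ordered ("The Markwalder classification divides the severity of symptoms of CSDH into 0–4"), but no mean difference is planned for it.
- *The analysis is declared unadjusted.* It is only silent on covariates, which an SAP commonly settles.
- *GCS will be compared in survivors only.* The article does not say how deaths enter the GCS comparison. That too is open for the SAP. Death is captured by mRS 6 and by the separate mortality endpoint.
- *Most patients will score near 15 at 6 months.* The documents do not say so. If it were so, equal variances would not hold, and the 1.33 to 1.67 range would not measure that situation.

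**Conclusion.** The inconsistency holds on the face of the document: GCS at 6 months is the endpoint, and change in GCS over unnamed visits is what is analysed. The two sections must be reconciled.

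The precision argument is secondary and conditional. Under equal variances and r from 0.2 to 0.5, a raw change score carries 1.67 to 1.33 times the variance of the baseline-adjusted comparison. Both assumptions come from outside the documents, and the size moves considerably if the SDs differ. The 4% to 33% for mRS rests on the same assumed range of r and on preoperative mRS being recorded.

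The missing Markwalder method is a note, not a finding. The primary endpoint, Fisher's exact test and the sample size are untouched.

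**What to change.** 1. In Secondary endpoints and in Statistical methods {20a}, name the same variable: GCS at 6 months. State the 6-month visit for mRS in the methods section as well.
2. Estimate the between-group mean difference in 6-month GCS adjusted for preoperative GCS, and keep the bootstrap 95% interval.
3. Apply the same adjustment to 6-month mRS if preoperative mRS is recorded. The Fig. 1 grid is not visible, so this needs checking.
4. As a note, give the Markwalder classification at 6 months a named analysis in the SAP.

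The cost is a few sentences in the methods section and the SAP, written before results by arm are examined. No new visit or patient is needed. Preoperative GCS is already required for minimisation; the data set must hold the score itself, not only the category at the 13/14 cut.
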